#### Follow-up

Treatment on-site visits will be performed at V2 (Week 6 ±5 days) and V3 (Week 14 ±5 days). An additional safety follow-up visit will be conducted by telephone at week 15 (±5 days). The assessments performed at each visit are summarized in Table 1. Adherence to background medication will be assessed by interview, and adherence to bempedoic acid will be assessed by pill count.

**Table 1 T1:** Study calendar.

Visit	Screening	Baseline	Treatment visits		Safety follow-up visit (by phone)
		V1	V2	V3^a^	V4^b^
Time	1–14 days prior to baseline	Day 0	Week 6 (±5 days)	Week 14 (±5 days)	Week 15 (±5 days)
Informed consent	x				
Inclusion/exclusion criteria	x				
Demographic data	x				
Medical history	x				
Physical examination/vital signs		x	x	x	
Quality of life questionnaire (SF-36)		x	x	x	
Lipid profile (including total cholesterol, HDL-C, LDL-C, and triglycerides)	x^c^		x	x	
Uric acid, creatine kinase	x^c^		x	x	
Dispense of study medication			X^d^		
Liver function test			x	x	
Serum *β*-hCG pregnancy test (patients of childbearing potential)	x		x	x	
Concomitant medication	x	x	x	x	
Adverse events				x^e^	x^e^
Return of IMP				x	

AEs, adverse events.

a Patients with LDL-C ≤ 2.8 mmol/L (110 mg/dL) will have a revisit (V3) 8 weeks after V2.

b Telephone inquiry regarding AEs after IMP discontinuation (triple therapy group) and equivalent time point for dual therapy group.

c Admission laboratory values from routine testing may be included within the screening period.

d Study medication will be given to patients with LDL-C ≥ 1.4 mmol/L (55 mg/dL). Patients with LDL-C > 2.8 mmol/L (110 mg/dL) will be directly recommended for PCSK9 inhibition.

e Triple therapy group and double therapy group from dispensation of IMP onward (V2).

All trial data will be entered into an Electronic Case Report Form provided by the Center for Clinical Trials, which will also conduct the monitoring.

#### Sample size

The number of patients for this study is based on previous experiences in secondary prevention surveys conducted at our institution (7). The primary objective of this study is to precisely estimate the proportion of patients who reach the ESC LDL-C guideline target of LDL-C < 1.4 mmol/L (55 mg/dL) after treatment Stage II in the triple therapy group. A sample size of *n* = 135 will enable us to estimate the responder rate with an accuracy of at least ±13.2%, corresponding to a confidence interval width of 26.4%. It is assumed that the responder rate is between *p* = 0.3 and *p* = 0.5. Since the standard deviation is maximal at *p* = 0.5, the confidence interval is the widest at *p* = 0.5. Hence, we assume a responder rate of 0.5 for a conservative sample size calculation. A small drop-out rate of 5% is expected in post-myocardial infarction patients. The primary analysis will be carried out in the intention-to-treat (ITT) population. For interpretation of the study results, analysis of the per-protocol (PP) population is also of clinical importance. To draw robust conclusions, consistency between ITT and PP results is needed. To account for potential drop-outs, we compute the sample size for the PP population. To determine an exact two-sided 95% Clopper–Pearson confidence interval with a width of 26.4%, assuming a responder rate *p* = 0.5, a sample size of 60 patients in the triple therapy group is needed.

Based on previous studies (7), approximately half of the enrolled patients will not achieve the goal of LDL-C < 1.4 mmol/L (55 mg/dL) during Stage 1. Because this is only an estimation and a drop-out rate of 5% is assumed, we will include up to 15 additional patients. This results in a total sample size of maximum 2*60 + 15 = 135 patients for the study, ensuring 60 patients complete the study period with bempedoic acid. This also means that recruitment will be stopped once 60 patients have continuously taken the investigational product and the background medication of atorvastatin (at least 40 mg/day, or equivalent) plus ezetimibe (10 mg/day) until V3, with blood tests completed at all visits.

All patients admitted to the Department of Cardiology with acute coronary syndrome will be screened for eligibility.

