## Background

Low-density lipoprotein cholesterol (LDL-C) is one of the most important modifiable cardiovascular risk factors (1). In 2019, European guidelines lowered the recommended target LDL-C from <1.8 mmol/L (70 mg/dL) to <1.4 mmol/L (55 mg/dL) for secondary prevention in coronary artery disease (2). Despite well-intended recommendations and strong evidence, the previous LDL-C target of <1.8 mmol/L (70 mg/dL) had only been achieved in 21% in of patients included in registries (3, 4). In Germany, the reported proportion was even lower, with ≤15% of patients achieving the target following an acute coronary syndrome (5, 6).

After broader availability of more potent statins such as atorvastatin and rosuvastatin, we recently assessed the achievement of LDL-C guideline targets in real-world everyday clinical practice postmyocardial infarction. In brief, early standardized potent lipid-lowering therapy with atorvastatin plus ezetimibe resulted in nearly every second patient discharged after ST-elevation myocardial infarction (STEMI) achieving an LDL-C < 1.4 mmol/L (55 mg/dL) (7), with even higher rates in those receiving high-dose potent statins combined with ezetimibe (8).

In addition to high-intensity potent statins plus ezetimibe, proprotein convertase subtilisin/kexin type 9 (PCSK9) inhibitors such as evolocumab or alirocumab have shown additive clinical benefit in cardiovascular outcome trials (9, 10), but are not widely available for the overall population due to prescription limitations. In Germany, oral combination therapy must be escalated to the maximum level with documented inefficiency to reach the guideline-recommended LDL-C target prior to prescription of PCSK9 inhibitors. In the meantime, bempedoic acid has demonstrated a significant reduction in cardiovascular events when used as an oral add-on therapy in case of statin intolerance (11). Beyond that, adding bempedoic acid to maximally tolerated statins in high-cardiovascular-risk patients results in a further reduction of LDL-C by 17% (12). Therefore, bempedoic acid may offer a potential option to achieve guideline-recommended LDL-C targets <1.4 mmol/L (55 mg/dL) when standard combinations of a potent statin and ezetimibe are insufficient, and is currently required as part of stepwise escalation treatment prior to PCSK9 inhibition.

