#### Study intervention/treatment

After the index hospitalization and enrolment into the trial, standard medication including atorvastatin (40 mg/day) and ezetimibe (10 mg/day) will be recommended. After 6 weeks (Stage I), a study visit will be conducted at the institution and another lipid test will be performed. Next (Stage II), study medication (bempedoic acid, 180 mg/day, provided by Daiichi Sankyo, Munich, Germany) will be given at V2 to patients with LDL-C 1.4-2.8 mmol/L (55-110 mg/dL) (Group A), and patients with LDL-C < 1.4 mmol/L (55 mg/dL) will be continued on the background medication with the previous dosing (Group B). Patients with LDL-C > 2.8 mmol/L (110 mg/dL) at week 6 will be directly referred for PCSK9 inhibition outside the trial. Patients with LDL-C ≤ 2.8 mmol/L (110 mg/dL) mg/dL will have a revisit (V3) after another 8 weeks, including another lipid test.

The dose of bempedoic acid— 180 mg/day—will not be modified. The background medication is atorvastatin (40 mg/day) plus ezetimibe (10 mg/day), which is the standard discharge medication. If—despite explanation about the study protocol—patients are escalated by their treating physicians to higher doses of atorvastatin (>40 mg/day) or switched to rosuvastatin (minimum 20 mg/day), this will be considered stable baseline medication with regard to the study protocol. Switching between medications and de-escalation of statin treatment are strongly discouraged. A sensitivity analysis excluding patients with escalated doses of atorvastatin or switching to equal doses of rosuvastatin is planned.

Remaining study medication will be counted upon return at V3. Aside from adherence to lipid-lowering therapy, no other restrictions apply to routine care.

This strategy reflects current guideline recommendations to either initiate or escalate to a dual lipid-lowering therapy with a high-dose potent statin in combination with ezetimibe prior to adding a third compound (17). It also supports the generalizability of HACOL-ACS results to broader patient populations.

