#### Study endpoints

The primary endpoint is defined as the proportion of patients (%) in Group A who successfully achieve the European Society of Cardiology (ESC) LDL-C guideline target after Stage II. Secondary endpoints comprise the following: proportion of patients (%) who successfully achieve ESC LDL-C guideline targets [LDL-C < 1.4 mmol/L (55 mg/dL)] after treatment with dual therapy including atorvastatin (at least 40 mg/day or equivalent) plus ezetimibe (10 mg/day) at 6 and at 14 weeks; the proportion of patients (%) who successfully achieve the ESC LDL-C guideline targets after 14 weeks of treatment; the proportion of patients (%) who achieve American heart Association (AHA)/American College of Cardiology (ACC) guideline-recommended treatment targets of LDL-C < 1.8 mmol/L (70 mg/dL) after 14 weeks of treatment in the triple therapy group; mean change from baseline to week 6 and week 14 in LDL-C, total cholesterol, HDL-C, triglycerides, uric acid, creatine kinase, systolic and diastolic blood pressure, and heart rate; the proportion of non-compliant patients (%) taking less than 90% of the allocated study medication; and mean change from baseline to week 6 and to week 14 in quality of life.

Safety will be assessed by monitoring and recording all adverse events, serious adverse events, and certain laboratory parameters (further described under pharmacovigilance).

The primary endpoint was chosen to focus on the efficacy of the investigational compound in order to prevent that a higher than anticipated achievement rate of the LDL-C target on the baseline medication might result in an escalation subgroup being too small to conduct proper statistical analyses.

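### The 135-patient cap does not ensure 60 bempedoic acid completers, and ±13.2 points is the precision for 60 evaluable patients, not for 135 enrolled

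*Protocol article*

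**What the plan says.** All the planning figures are in the Sample size section of the protocol article.

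- **Precision.** A sample of 135 "will enable us to estimate the responder rate with an accuracy of at least ±13.2" percent. The same section then derives that width for a smaller number: for an exact 95% Clopper–Pearson interval at a responder rate of 0.5, "a sample size of 60 patients in the triple therapy group is needed". The 60 is computed for the per-protocol population.
- **Yield.** The plan expects that "approximately half of the enrolled patients will not achieve the goal of LDL-C < 1.4 mmol/L (55 mg/dL) during Stage 1", and that 5% drop out. It allows up to 15 further patients for both, which gives 2 × 60 + 15, a maximum of "135 patients for the study, ensuring 60 patients complete the study period with bempedoic acid".
- **Stopping.** Recruitment ends once 60 patients have taken both the study drug and the background medication continuously to V3, with all blood tests done.
- **An exit before Group A.** Study intervention/treatment says: "Patients with LDL-C > 2.8 mmol/L (110 mg/dL) at week 6 will be directly referred for PCSK9 inhibition outside the trial". These patients miss the target but never enter Group A.
- **Primary analysis.** Under Statistical analysis, the primary analysis is ITT, and missing primary endpoint values count as failures.

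**The concern.** The plan presents as certain something that depends on a random count. It needs 60 completers, enrols at most 135, and relies on about half of them missing the target and on few dropping out. The 15 extra patients raise the expected number of completers above 60 but do not guarantee 60. The precision figure is also attached to the number enrolled rather than to the number analysed.

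The calculation further treats every patient not at target as a candidate for Group A, although those above 2.8 mmol/L at week 6 are referred out of the trial.

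The study is single-arm and descriptive, and its stated primary objective is precise estimation of one proportion. The precision statement is therefore its main planning claim, and readers should be able to take it at face value.

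**Working it through.** **Inputs from the Sample size section:** maximum enrolment 135; 60 completers needed; share not at target after Stage I 0.5; drop-out 0.05; planning responder rate 0.5 (assumed range 0.3 to 0.5); two-sided 95% Clopper–Pearson interval.

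**1. The plan's own figures.** With x = 30 and n = 60, the limits are the 2.5% point of Beta(30, 31) and the 97.5% point of Beta(31, 30): 0.3681 and 0.6319. The width is 26.39%, or ±13.2 points. Also 2 × 60 + 15 = 135. Both reproduce. If all 135 were in the denominator, the width would be 17.4% (±8.7 points), so ±13.2 is a property of 60 patients.

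**2. Completers (the per-protocol count).** The chance that an enrolled patient becomes a triple-therapy completer is q = 0.5 × 0.95 = 0.475.

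- Expected completers: 135 × 0.475 = 64.1.
- Enrolment at which 60 are expected on average: 60 / 0.475 = 126.3.
- Binomial tail: P(X ≥ 60 | 135, 0.475) = 0.787, which leaves about a 21% chance of falling short.

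Removing the 5% first and then halving gives nearly the same: 0.787 with 128 left, 0.811 with 129 left.

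**3. Primary ITT Group A.** If drop-outs occur after V2, they stay in the denominator as failures, so q = 0.5. Expected size is 67.5 and P(X ≥ 60 | 135, 0.5) = 0.916.

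**4. Direct referrals.** Let r be the share of all enrolled patients above 2.8 mmol/L at week 6. The article gives no value, so 2% and 5% are assumptions that show the direction and rough size. Completers have q = (0.5 − r) × 0.95; ITT Group A has q = 0.5 − r.

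| r | Expected completers | P(≥ 60 completers) | P(ITT Group A ≥ 60) |
|---|---|---|---|
| 0 | 64.1 | 0.787 | 0.916 |
| 2% (assumed) | 61.6 | 0.638 | 0.819 |
| 5% (assumed) | 57.7 | 0.377 | 0.584 |

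**5. What a shortfall costs.** Clopper–Pearson width at an observed rate of 0.5; the percentiles are those of the completer count from 135 at q = 0.475.

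| Evaluable | Width | Half-width (points) | Position under the stated assumptions |
|---|---|---|---|
| 60 | 26.4% | ±13.2 | planned |
| 57 | 27.1% | ±13.5 | 10th percentile |
| 55 | 27.6% | ±13.8 | 5th percentile |
| 51 | 28.7% | ±14.3 | 1st percentile |
| 50 | 28.9% | ±14.5 | probability 0.009 of 50 or fewer |

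For odd n the exact half is not an integer count; the nearest integer count gives the same width to one decimal.

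**The case against.** The best defence is that no stated sum is wrong and that little precision is at risk. That largely stands. Under the plan's assumptions the half-width at the 5th percentile is 0.6 points wider than planned, and 45 or fewer completers has probability 0.0006. Planning at 0.5 is also conservative: at an observed rate of 0.3, 52 patients already give a width of 26.2%. The study is exploratory with no test or power at stake, Trial status gives recruitment as July 2023 to March 2026, and the final interval will show its own width.

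Several stronger readings are tempting, but the documents do not support them.

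- **That the primary analysis has only a 79% chance of 60 patients.** The 79% concerns per-protocol completers. ITT Group A reaches 60 with about 92% probability before referrals.
- **That dual-therapy success will probably exceed half and shrink Group A.** The Background section does report success "with even higher rates in those receiving high-dose potent statins combined with ezetimibe", but the standard background medication here is atorvastatin 40 mg/day plus ezetimibe. For atorvastatin plus ezetimibe the article reports nearly every second patient at target, which is slightly under half and favours the plan: an assumed 48% at target gives a 0.89 chance of 60 completers.
- **That non-compliance must be deducted as well.** The article gives no rate and does not define the per-protocol set, so non-compliance may already be inside the 5%.
- **That the reason given for the primary endpoint is backwards.** Study endpoints says the choice guards against a high success rate on background therapy that "might result in an escalation subgroup being too small to conduct proper statistical analyses". Making Group A primary means recruitment is sized and stopped on Group A completers, which does protect its size up to the cap. The sentence is awkward, not shown to be wrong.
- **That the end of recruitment is undefined.** The stated maximum and the stopping rule together already imply whichever comes first.

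What the defence does not answer is that a capped design with a 79% chance of 60 completers does not ensure them, and that ±13.2 is attached to the wrong n.

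**Conclusion.** The point holds as a minor overstatement. The ±13.2 points is correct for 60 evaluable triple-therapy patients at a responder rate of 0.5. With 135 enrolled, 50% not at target and 5% drop-out, the chance of at least 60 is about 79% for per-protocol completers and about 92% for ITT Group A, the latter assuming that drop-outs occur after V2. Both are upper figures with respect to direct referrals, which the calculation leaves out. An assumed 2% to 5% of enrolled patients referred lowers the completer probability to about 64% to 38%, but no referral share is documented. A reader might infer that the trial will be seriously imprecise; under the stated assumptions the half-width is about ±13.8 points at the 5th percentile. About ±14.5 points, at 50 evaluable, would realistically arise only if referrals, non-compliance or dual-therapy success exceed what was assumed.

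**What to change.** Reword the Sample size section:

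- State that precision is ±13.2 points (95% Clopper–Pearson, responder rate 0.5) if 60 triple-therapy patients are evaluable, and detach that figure from n = 135.
- Replace the claim that 135 ensures 60 completers with: under 50% not at target and 5% drop-out, 135 enrolled give about a 79% chance of at least 60 per-protocol completers and about 92% for ITT Group A, before direct referrals.
- State that patients referred out at V2 lower both figures, and give the referral share if one can be justified.
- Give the half-width if the cap binds: about ±13.5 points at 57 and ±13.8 at 55 evaluable under the stated assumptions, and ±14.5 at 50 if losses exceed them.

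The endpoint rationale and the stopping rule need no change. The cost is a few sentences and a slightly less favourable precision statement. No extra patients and no change to the analysis are needed.

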## Statistical analysis

All analyses will be descriptive and performed in the ITT population. Demographic and baseline measurements will be summarized using descriptive methods. In the primary analysis, the proportion of responders and an exact descriptive 95% Clopper–Pearson confidence interval (CI) will be calculated. Patients with missing values for the primary endpoint will be counted as treatment failures in the ITT analysis, that is, as patients who did not achieve LDL-C guideline targets of <1.4 mmol/L (55 mg/dL) after treatment for 14 weeks.

Explanatory analyses for secondary endpoints will be carried out separately for Groups A and B. Responder rates will be examined using the exact 95% Clopper–Pearson CIs, and continuous data will be compared exploratorily using two-sided paired *t*-tests, with a two-sided level significance of 5%. In addition, mean changes in continuous laboratory parameters will be compared between Groups A and B using an analysis of covariance model, including baseline values at the start of the study and group assignment.

For the primary endpoint, a subgroup analysis will be carried out. Patients in the triple therapy group who fail to achieve the LDL-C guideline target of LDL-C < 1.4 mmol/L (55 mg/dL) after Stage I will be divided into four subgroups depending on their LDL-C level:
Group: LDL-C of 55 – ≤ 68.75 mg/dL (1.4–≤1.8 mmol/L).Group: LDL-C of 68.75 – ≤ 82.5 mg/dL (1.8–≤2.1 mmol/L).Group: LDL-C of 82.5 – ≤ 96.25 mg/dL (2.1–≤2.5 mmol/L).Group: LDL-C of 96.25 – ≤ 110 mg/dL (2.5–≤2.8 mmol/L).In every subgroup, the proportion of responders will be examined and exact 95% Clopper–Pearson CIs will be calculated. To evaluate the robustness of the results, efficacy analyses will be repeated in the PP population (sensitivity analyses).

Descriptive analyses will be performed to assess adverse events and serious adverse events. As this is an exploratory study, no adjustment for multiplicity will be performed. Confidence intervals and respective *p*-value will only be assessed descriptively.

Access to the final trial dataset will be centralized at the Center for Clinical Trials.

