**Methods:**

This is a prospective, interventional, single-center study designed to assess the effectiveness of bempedoic acid in achieving LDL-C targets in patients following ST-elevation or non-ST-elevation myocardial infarction who remain insufficiently treated with atorvastatin plus ezetimibe. Patients not previously treated with lipid-lowering agents and presenting with admission LDL-C > 2.6 mmol/L (100 mg/dL) will be treated with atorvastatin (at least 40 mg/day or equivalent) plus ezetimibe (10 mg/day) for 6 weeks. Thereafter, the subgroup of patients failing to reach an LDL-C < 1.4 mmol/L (55 mg/dL) will be escalated to additive bempedoic acid (180 mg/day) for another 8 weeks. Those who reach the target will continue the aforementioned therapy. The primary endpoint is the proportion of patients who successfully achieve an LDL-C < 1.4 mmol/L (55 mg/dL) after 8 weeks of treatment with triple therapy. Secondary endpoints include the proportion of patients successfully reaching the target in the overall population and in the background medication group alone.

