We planned and initiated the HAnnover ChOlesterol Lowering in Acute Coronary Syndrome (HACOL-ACS) trial to address three major clinically relevant questions: First, how many patients after a myocardial infarction reach the guideline-recommended target [LDL-C < 1.4 mmol/L (55 mg/dL)] on dual therapy with atorvastatin (at least 40 mg/day or equivalent) plus ezetimibe (10 mg/day)? Second, how many of the patients not achieving the target on a dual statin/ezetimibe therapy reach the target after adding bempedoic acid? Third, how many patients miss the target despite escalated oral triple lipid-lowering therapy and therefore need referral for PCSK9 inhibition? Our trial is distinct from the ES-BempedACS trial, as it focuses exclusively on patients without previous lipid-lowering therapy and will demonstrate the exact additive impact of bempedoic acid on top of dual therapy in each patient due to its sequential escalation strategy. Thereby, we will evaluate the real-world, guideline-mandated stepwise oral escalation therapy and quantify the residual unmet need for LDL-C target achievement. Starting with dual background medication is consistent with current guideline recommendations (17), and sequential add-on with bempedoic acid is also guideline-recommended (17), although this approach has never been tested in clinical practice. It is therefore important to document the efficacy of additive bempedoic acid on top of established and tolerated high-intensity statin treatment in combination with ezetimibe, to provide data supporting such recommendations. This is particularly important for the trial to be conducted in a sequential and clear manner as recent data from the ES-BempedACS trial with varying pretreatment populations did not show an additive LDL-C-lowering effect of bempedoic acid (15). Similarly, data from a recent oral PCSK9 inhibitor trial showed only a marginal additive effect in the bempedoic acid-treated comparator group when added to stable statin therapy (18).

The results of HACOL-ACS will also provide meaningful information for patients beyond the German healthcare system. While the trial design is adapted to national settings, the proportion of patients achieving guideline-recommended LDL-C targets at the end of the trial with double and triple therapies will be applicable both in regions with sequential dose escalations and in those allowing triple therapy from the beginning.

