**Figure 1 F1:**
[figure not shown]
Study algorithm. eGFR, estimated glomerular filtration rate; Hx, History of …; LDL-C, low-density lipoprotein-cholesterol; NSTEMI, Non-ST-segment myocardial infarction; STEMI, ST-segment myocardial infarction.

Group A will consist of the subgroup of patients who do not reach the LDL-C guideline target [LDL-C < 1.4 mmol/L (55 mg/dL)] after 6 weeks and will receive additive bempedoic acid (180 mg/day) for another 8 weeks (Triple therapy). Group B will consist of the subgroup of patients who achieve the LDL-C guideline target after 6 weeks of treatment with atorvastatin plus ezetimibe and who will continue on dual therapy for another 8 weeks (Dual therapy).

The 6-week escalation interval reflects local healthcare system, including certain reimbursement constraints, while aligning with evidence-based preferences to minimize delays in treatment intensification.

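### Secondary endpoints are to be analysed by group, but the groups are defined by the week-6 LDL-C result, so the stated rule yields 0% and 100% at week 6 and no whole-cohort rate with a fixed denominator

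*Protocol article*

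**What the plan says.** All references are to the protocol article.

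- **Group definitions** (Study design, below Figure 1): "Group A will consist of the subgroup of patients who do not reach the LDL-C guideline target" after 6 weeks, while "Group B will consist of the subgroup of patients who achieve the LDL-C guideline target after 6 weeks of treatment". Study intervention/treatment narrows Group A to 1.4–2.8 mmol/L. It sends patients above 2.8 mmol/L at week 6 for PCSK9 inhibition outside the trial, without a V3.
- **First question** (Background): "how many patients after a myocardial infarction reach the guideline-recommended target" on dual therapy.
- **Secondary endpoints** (Study endpoints): target attainment "after treatment with dual therapy including atorvastatin (at least 40 mg/day or equivalent) plus ezetimibe (10 mg/day) at 6 and at 14 weeks", and separately "the proportion of patients (%) who successfully achieve the ESC LDL-C guideline targets after 14 weeks of treatment", with no group named. The list also has mean changes from baseline to weeks 6 and 14.
- **Abstract, Methods:** secondary endpoints include "the proportion of patients successfully reaching the target in the overall population and in the background medication group alone".
- **Analysis rule** (Statistical analysis): "Explanatory analyses for secondary endpoints will be carried out separately for Groups A and B". Responder rates get exact Clopper–Pearson intervals, and mean changes in laboratory values are compared between A and B by analysis of covariance. All analyses are in the ITT population. The rule that a missing value counts as failure is written for the primary endpoint.

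**The concern.** A group defined by an outcome cannot be used to estimate the rate of that outcome. Membership of A or B is the week-6 target result, so reporting that result within A and within B returns the definition and nothing about dual therapy.

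Three other results are affected by the same rule:

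- The overall week-14 rate needs the whole cohort, which a by-group analysis does not supply.
- The dual-therapy rate at 14 weeks can come only from Group B, since only those patients are still planned to be on dual therapy. It is conditional on success at week 6, so it measures maintenance of the target and not the success rate of 14 weeks of dual therapy.
- Baseline-to-week-6 change in LDL-C, split or compared by group, contrasts patients sorted on the end value of that same change. All had the same planned background regimen until V2.

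At stake are a headline question of the trial and a listed overall endpoint. Both depend on a denominator that the written rule does not set.

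**Working it through.** **1. The plan's own figure.** The exact interval for x of n has lower limit Beta(0.025; x, n−x+1) and upper limit Beta(0.975; x+1, n−x). For 30/60 this gives 36.81% to 63.19%, a width of 26.39%. That reproduces the 26.4% in the Sample size section; n = 59 gives 26.61%. The same method is used below.

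**2. The rule as written, at week 6.** By definition the rate is 0/n in A and n/n in B. With an illustrative 60 per group:

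- A: 0/60, upper limit 1 − 0.025^(1/60) = 6.0%, so 0% to 6.0%.
- B: 60/60, lower limit 0.025^(1/60) = 94.0%, so 94.0% to 100%.

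These intervals depend only on the group sizes.

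**3. The pooled analysis.** The Sample size section expects about half of enrolled patients to miss the target in Stage I, so take p = 0.5.

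| N | Exact 95% interval | Width |
|---|---|---|
| 135 (maximum) | 41.3% to 58.7% | 17.4 points |
| 120 (2 × 60) | 40.7% to 59.3% | 18.5 points |

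For N = 135 the count is taken as 67.5; 67 or 68 patients give the same width. N = 120 is shown because 135 is a ceiling: recruitment stops once 60 patients have completed triple therapy.

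**4. The denominator.** The week-6 rate can be rebuilt as n(B)/N. If Group A is limited to 1.4–2.8 mmol/L, patients above 2.8 mmol/L are in neither group, and patients without a V2 value cannot be classified at all. None of them is in B, so omitting k of them leaves the numerator alone and shrinks the denominator: rate = n(B)/(N − k).

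Assumed example, n(B) = 64 and N = 135:

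| k omitted | Rate | Exact 95% interval |
|---|---|---|
| 0 | 64/135 = 47.4% | 38.8% to 56.2% |
| 5 | 64/130 = 49.2% | 40.4% to 58.1% |
| 10 | 64/125 = 51.2% | 42.1% to 60.2% |
| 15 | 64/120 = 53.3% | 44.0% to 62.5% |

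The range for k is an assumption. The plan's 5% drop-out would be 135 × 0.05 = 6.75, about 7 patients, if all were lost before V2. The number above 2.8 mmol/L is not given.

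**5. Week 14.** The overall rate is (A at target at V3 + B at target at V3)/N. The by-group rule gives the two numerators over their own group sizes, and patients above 2.8 mmol/L have no V3 by design. The missing-as-failure rule, written for the primary endpoint, does not say how they count here.

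**The case against.** The strongest reply is that this is one loosely drafted sentence in an exploratory, descriptive study. Study endpoints lists the week-6 rate, the abstract names the overall population, and all analyses are placed in the ITT population. Any report of the group sizes shows the week-6 rate. The article condenses a fuller protocol, and an analysis plan may already specify pooled tables.

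Much of this stands, and it rules out several stronger readings that a reader might infer:

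- **That the first question goes unanswered.** It does not: n(B)/N answers it once N is fixed.
- **That the overall week-14 rate will not be reported.** The abstract and the endpoint list both commit to it. The by-group sentence conflicts with that commitment but does not cancel it.
- **That Group B's week-14 rate will look like a gain over week 6.** Under the by-group rule Group B starts at 100%, so its rate can only hold or fall.
- **That the distortion in the by-group changes can be sized.** That needs the spread and within-person variability of LDL-C on treatment, which the documents do not give. Only the direction is supported.

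It is also fair that Group B's selection is openly stated, so calling its week-14 rate maintenance is a matter of clear labelling.

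What does not fall away is that the article states a rule, and that rule gives an uninformative result for a listed endpoint and disagrees with other sections. The general reference to ITT does not say how patients above 2.8 mmol/L or without a V2 value count.

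**Conclusion.** The point holds as a conflict between the stated analysis rule and the listed endpoints. By group, the week-6 target rate is 0% and 100% by construction, and neither the whole-cohort week-6 rate nor the overall week-14 rate comes out of the rule. This follows from the definitions and needs no assumption.

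The practical size lies in the denominator. In the assumed example the week-6 rate rises from 47.4% by 1.8 to 5.9 points when 5 to 15 unclassified patients are left out. That depends on the assumed counts; the upward direction does not.

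The primary endpoint, its interval and the sample size are untouched, and no data are lost. This is a should-fix.

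**What to change.** Replace the by-group sentence in Statistical analysis with wording to this effect:

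1. Week-6 target attainment, baseline-to-week-6 changes and the overall week-14 target rate are each estimated once in all enrolled (ITT) patients, with exact Clopper–Pearson intervals for the two rates.
2. For the week-6 rate, patients with a missing V2 value count as not at target. Patients above 2.8 mmol/L stay in the denominator as not at target.
3. For the overall week-14 rate of the oral strategy, patients above 2.8 mmol/L at week 6 and patients with a missing V3 value count as not at target. The number above 2.8 mmol/L is reported separately, because their missing V3 is planned.
4. By-group analysis, including the A-versus-B analysis of covariance, is limited to Stage II (V2 to V3). It remains descriptive, since the groups are formed on the V2 value.
5. The Group B week-14 rate is described as maintenance of target among week-6 responders.

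The two descriptions of Group A (all who miss the target, or only those at 1.4–2.8 mmol/L) should be reconciled at the same time.

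The cost is a wording change in the analysis and reporting text, made before the analysis is run. It needs no new data. The downside is that the reported rates will be slightly less favourable.
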